### Measures

#### Baseline measures

Baseline data will be collected by an online questionnaire using the Tencent Questionnaire platform, including demographic information, smoking history, previous quit attempts, and comorbidities, etc. Nicotine dependence is measured by the Fagerstrӧm test for nicotine dependence (FTND) [39].

#### Follow-up measures

All participants will complete 1-, 3-, 6-, and 12-month follow-up assessments over the phone or online using the Tencent Questionnaire platform at participants’ convenience. Three non-participating staff will conduct the telephone follow-ups. The follow-up assessment information includes smoking status, quitting attempts, acceptability and satisfaction of the cessation services, and the usage of smoking cessation services, etc. A scale of 0 to 10 (0: not at all; 10: very high) for acceptability and satisfaction with each service will be evaluated. Participants who report quitting smoking or reducing their consumption of cigarettes will fill out the Minnesota Nicotine Withdrawal Scale (MNWS) [40] and the Brief- Questionnaire of Smoking Urges (QSU Brief) [40]. Adverse events and other unintended effects of interventions during the intervention period will be spontaneously reported. At 1-month follow-up, individuals with self-reported smoking abstinence for more than 7 days will be invited to participate in an exhaled carbon monoxide (CO) test for biochemical validation. To increase follow-up compliance, participants will receive 100 RMB (approximately US $ 14.95) in the form of the WeChat red packet (Hongbao, which is similar to an electronic cash reward [41]). The full list of measurements is presented in Table 3.

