### Interventions

#### Quitline-based treatment (QT group)

Participants in the QT group will receive standard proactive quitline services from China Professional Quitline ([name]) for 4 weeks using a multi-call quitline protocol [19]. The first session will focus on quitting history, motivation, self-efficacy, social support, and planning in advance of the quitting date. Smokers will be reminded in the second session to quit smoking completely from the quitting date, be provided with the practical information on how to quit. The sessions followed the quitting date (up to three sessions) will focus on building cessation skills and relapse prevention. Three Chinese-speaking counselors will provide the quitline services. All of them possess at least a bachelor’s degree in medicine or nursing, and have received more than 60 h of training in smoking cessation counseling.

To improve the participants’ adherence of the quitline intervention protocol, the counselors will call them at three time points for three consecutive days during each session, arrange the next session time for the participants, and contact the participants’ relatives and friends whenever necessary.

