#### Other interventions

All participants will receive a 4-week supply of NRT gum by mail (300 pieces). The gum is FDA-approved Nicorette brand 2 mg nicotine mint gum (McNeil Sweden AB, Inc., Helsingborg, Sweden). Participants will be directed to use the gum as needed when they encounter situations or cues that tempt them to smoke, or in anticipation of such situations [38]. A smoking cessation material with a video link to the instruction of medication use will be mailed with the gum.

After receiving the allocation interventions for 4 weeks, participants in the QT group will receive reactive smoking cessation counseling via telephone for one year, and participants in the WQ group will also receive the reactive counseling via the WeChat group. Smoking cessation interventions other than the allocated intervention are prohibited during the study, such as bupropion, varenicline, electronic cigarettes and other mHealth-based tools, such as web, SMS texting, apps, etc.

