### Data management

Data from all questionnaires and assessment scales will be collected electronically via the Tencent questionnaire platform. These data will be integrated with data on the use of smoking cessation services downloaded from the Quitline and WeChat platforms. Participants' cell phone numbers were used as unique identifiers.

All study files will be stored securely in password-protected computer files. Only the principal investigators of the study ([name] and [name]) will be given access to the cleaned full data sets. A data monitoring committee (DMC) has been established and composed of clinicians and statisticians independent of clinical trials, which will be responsible for monitoring study conduct, safety, effectiveness and adaptive design. It is independent from the sponsor and has no role in the design of this study and will not have any role during its execution, analyses, interpretation of the data, or decision to submit results.

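### Adverse events rest on spontaneous reporting alone, so counts are likely to be low in both arms and may be captured unequally; one common question at 1 month would address this.

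*Protocol article*

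**What the plan says.** The Follow-up measures section gives the method and the window in one sentence: "Adverse events and other unintended effects of interventions during the intervention period will be spontaneously reported". The same section lists what the follow-up contacts collect: "The follow-up assessment information includes smoking status, quitting attempts, acceptability and satisfaction of the cessation services, and the usage of smoking cessation services, etc". Adverse events are not in that list, though it is open-ended and refers to Table 3, which is not visible.

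The follow-up schedule is common to both arms: "All participants will complete 1-, 3-, 6-, and 12-month follow-up assessments over the phone or online". Those who report having quit or cut down "will fill out the Minnesota Nicotine Withdrawal Scale (MNWS").

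Both arms receive the same drug. Under Other interventions: "All participants will receive a 4-week supply of NRT gum by mail (300 pieces"). Under Data management, a data monitoring committee (DMC) is "responsible for monitoring study conduct, safety, effectiveness and adaptive design".

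**The concern.** Spontaneous reporting records only what a participant thinks worth mentioning and finds an occasion to mention. Mild or expected complaints are the ones most easily lost. Here the gum comes by post, eligibility is screened by online questionnaire, and no routine visit is described. The only in-person step apparent in the text is the carbon monoxide test at 1 month, offered to self-reported abstainers only.

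The occasions for mentioning a complaint also differ by allocated arm, and the trial is open label. If the chance of capture differs, a difference in recorded events could appear with no difference in true risk, or a true difference could be hidden. At stake are the completeness of the safety record and the reading of any harms table split by arm. The primary abstinence comparison is not affected.

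**Working it through.** **1. Is this a stated choice or a gap left to a fuller document?** It is stated. The article names the method (spontaneous) and the window (the intervention period, four weeks). The unseen Table 3 might add a question, but the text as written does not describe one.

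**2. Do the routes of capture differ by arm?** Set side by side from the two intervention sections, Table 1, Table 2 and Service usage data:

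| | QT | WQ |
|---|---|---|
| Live contact | One-to-one calls: a first, a second and up to three more, so 1 + 1 + 3 = 5 at most | Group chat with three counsellors and an administrator; weekday question sessions, about 5 × 4 = 20 slots; phone reminders to low users |
| Automated contact | None described | One message a day for four weeks from the quit date, 7 × 4 = 28 |
| Prompt about side effects | None described | Mini-program medication module asks about them |
| Described recording | Number, length and content of calls | Registration, logins, time in group and message counts; content not mentioned |

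For QT the later calls are described thus: "The sessions followed the quitting date (up to three sessions) will focus on building cessation skills and relapse prevention". To reach people, "the counselors will call them at three time points for three consecutive days during each session".

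The routes do differ, but not all in one direction. The side-effect prompt and the open chat favour capture in WQ. Private calls with recorded content favour capture in QT.

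**3. How much could this matter?** The article gives no event risk and no reporting probability, so these are assumptions. Recorded rate = true risk × probability of capture. With a true risk of 20% in both arms:

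- capture 60% and 30%: 0.20 × 0.60 = 12%; 0.20 × 0.30 = 6%
- capture 60% and 50%: 0.20 × 0.60 = 12%; 0.20 × 0.50 = 10%
- capture 30% in both: 0.20 × 0.30 = 6% in each

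**4. Chance of a spurious significant difference.** This uses n = 230 per arm from the Sample size section and a two-sided 5% test. That n is consistent with the plan's own inputs: 20% against 35% at 90% power gives 181 to 185 per arm, and dividing by 0.80 gives 227 to 232.

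With recorded rates p1 and p2 and mean p, the chance is Φ{[|p1 − p2|√n − 1.96√(2p(1 − p))] / √(p1(1 − p1) + p2(1 − p2))}.

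For 6% and 12%: |p1 − p2|√n = 0.06 × 15.166 = 0.910; 1.96 × √(2 × 0.09 × 0.91) = 0.793; denominator √(0.0564 + 0.1056) = 0.402. So Φ(0.29) = 61%.

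| True risk, both arms | Capture 60% and 30% | Capture 60% and 50% |
|---|---|---|
| 10% | 6% v 3%; chance 34% | 6% v 5%; chance 7% |
| 20% | 12% v 6%; chance 61% | 12% v 10%; chance 10% |
| 30% | 18% v 9%; chance 81% | 18% v 15%; chance 14% |

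The figures are the same whichever arm has the higher capture. With equal capture there is no distortion between arms, only under-counting.

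**The case against.** The strongest case against is that the reporting rule, the follow-up times and modes, and the follow-up staff are the same in both arms. Adverse events are not among the listed outcomes and no between-arm comparison of them is planned. Both arms get the same gum, so gum complaints are not a treatment contrast. The withdrawal scale is solicited in both arms, people with conditions ruling out nicotine replacement are excluded, and severe withdrawal has its own referral route. Table 3 and the full protocol may hold more.

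Much of this stands, and it rules out several stronger readings that a reader might infer:

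- *WQ has far more contact, so WQ will report more.* WQ has more touchpoints, but many are automated or in a group chat, while QT contact is live, private and recorded. The direction is open.
- *The arms are not comparable.* This would need a capture gap that the article neither states nor allows to be estimated. It is a possibility only.
- *Events are known only if volunteered.* The WQ side-effect module and the withdrawal scale do solicit symptoms, though neither is described as a source of adverse-event data.
- *The DMC must judge safety from these reports alone.* The article does not say what data the committee receives.

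The objection does not answer the under-counting. The withdrawal scale goes only to those who quit or cut down, a group formed after randomisation that the trial itself expects to differ in size by arm. It measures withdrawal, not adverse events in general.

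**Conclusion.** The point holds in a limited form. Spontaneous reporting is the stated method, and it is likely to record too few events in both arms. Recorded counts may also be ascertained unequally, because prompts, occasions and record-keeping differ by arm, but neither the size nor the direction of that inequality can be settled from the article.

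The under-counting conclusion rests on the general weakness of unprompted reporting and on no adverse-event question appearing in the unseen Table 3. The between-arm figures rest wholly on assumed risks and capture rates. They range from no distortion with equal capture to a doubling of the recorded rate in one arm. This is a low-priority improvement with no bearing on the primary analysis.

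**What to change.** Add one adverse-event question, worded identically for both arms and for phone and online completion, to the planned 1-month follow-up. It should ask about the four-week intervention period, which that contact closes. Report elicited events by arm, with the number who answered as denominator, separately from spontaneous reports. If Table 3 or the full protocol already contains such a question, correct the sentence in Follow-up measures to say so.

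The cost is one extra item and more minor events to record and code. Recruitment began in December 2022, so participants already past 1 month would have no elicited data. Introducing the question in both arms on the same date keeps the later comparison fair. Treatment, sample size and the primary outcome are unchanged.

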### Participants and recruitment

Participants will be Chinese smokers. The inclusion criteria are: 1) 18–65 years of age; 2) smoked at least 100 cigarettes in lifetime; 3) currently smoke at least 5 cigarettes per day; 4) willing to make a quit attempt within 1 month; 5) possess a smartphone and a WeChat account, and could operate WeChat app skillfully; 6) promise to complete follow-up on time. Exclusion criteria include: 1) difficulty in understanding the questionnaire; 2) acute exacerbation of chronic cardiopulmonary disease; 3) having received coronary surgical interventions (such as coronary angiography, percutaneous coronary interventions, etc.) in the last month or will receive these interventions in the next month; 4) discharge within 1 month; 5) medical conditions that preclude the use of nicotine replacement therapy (NRT); 6) currently using smoking cessation medications or other aids, including NRT, bupropion, varenicline, electronic cigarettes and other mHealth-based tools, such as web, SMS texting, apps, etc.; 7) being enrolled in another smoking cessation study.

Eligible participants will be recruited through online advertisement. Individuals who are interested in participating will screen a Quick Response (QR) cord to complete a screening questionnaire to ascertain their eligibility for the study. Eligible individuals will be provided an electronic consent (e-consent) form online. After reading the e-consent, they should click the agree button at the end of the form to indicate their consent to participate in the study. The participant recruitment has been started since December 15, 2022, and is ongoing.

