### Statistical analysis plan

All statistical analyses be analyzed and blinded to the intervention assignment by a statistician using SPSS version 22.0 software (SPSS, Inc., Chicago, IL). Data will be presented as mean (standard deviations) for continuous variables with normal distribution; median (inter-quartile range) for continuous variables without normal distribution; and proportions for categorical variables. Baseline characteristics of participants in the intervention and control groups will be compared using Student’s t-test or non-parametric test for continuous variables and Pearson's chi-square or Fisher's exact test for categorical variables.

Multiple logistic regression will be used for between-group comparisons of the primary outcome variable-biochemically validated 7-day PPA at the 1-month follow-up and the secondary outcomes- self-reported 7-day PPA at the 1-, 3-, 6-, and 12-month follow-up and self-reported continuous smoking abstinence from 1-month to 12-month, with odds ratio (OR) and 95% confidence intervals (CI) to assess between-group effects. By intent-to-treat analysis (ITT), participants who are lost to follow-up or refuse to participate in the validation tests will be considered as continuing smokers with no reduction in cigarette consumption compared with baseline. Participants who do not use smoking cessation services after randomization will be excluded from the ITT analysis data set. In addition, we will conduct a per-protocol (PP) analysis of the primary outcome among the participants in the QT group who receive at least one telephone session and those in the WQ group who use the QUIT WMP for at least 20 days and send more than 10 short messages in the QUIT WG. For comparisons of secondary continuous outcomes with non-normal distribution assumptions, Mann–Whitney tests will be conducted. Subgroup analyses will assess the efficacy in participants with different demographics, baseline smoking characteristics, combined chronic diseases, and use of intervention variables (including compliance of using NRT gum, frequency and duration of using WeChat- or quitline-based cessation services) using multiple logistic regression. No interim analysis will be conducted. A two-sided *P* value of < 0.05 will be considered as statistically significant difference.

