The primary outcome of this study is slightly different from that of other related studies. The Society for Research on Nicotine and Tobacco recommends that the effectiveness outcome at the end of the intervention should be the primary outcome for determining whether the treatment is effective [42]. In light of this, we choose the short-term (1-month) outcome as the primary outcome based the intervention period (four weeks) rather than the long-term (such as 6-months or 12-months) outcomes selected by other studies [55]. Nevertheless, most of other studies have reported 1-month outcome [55], and we will also collect the long-term (3-month, 6-month, and 12-month) outcomes as secondary outcomes. Thus, the results of this study will be comparable to those of other studies.

Limitations should be mentioned. Firstly, the intervention period in this study has a shorter intervention period (four weeks) than other related studies (more than three months) [55]. This is primarily due to the relatively low engagement of mHealth-based approaches over a prolonged period, and the highest activity often occurs in the first month [56]. In the future, we will extend the intervention period once the effectiveness of this short-term intervention modality has been confirmed, with the intention of improving the long-term effectiveness of the WQ modality. Secondly, this study is an open label study, which may lead to information bias. In order to compensate for this type of bias, a variable random block length can be used instead of a fixed length, such as four or six. Furthermore, the staff performing the telephone follow-ups and statistical analysis will be blinded, and the participants’ self-reported abstinence will be biochemically validated by the exhaled CO test. Thirdly, this is a single-center study which could limit the generalizability of the results. Finally, all participants will be young to middle-aged, as elderly individuals have difficulty utilizing mobile devices skillfully [57]. Accordingly, the results should be extrapolated with caution to the elderly population.

It is anticipated that this trial, along with its findings will provide evidence for the WQ modality as an effective, acceptable, and affordable mHealth-based approach to smoking cessation. It will be of paramount significance to reduce health disparities as well as address the imbalance in smoking cessation services between regions and socioeconomic groups.

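### Adverse-event reporting is worded to stop with the four-week intervention period, although the as-needed trial gum can still be in use after it

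*Protocol article*

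**What the plan says.** The safety rule is one sentence under Follow-up measures: "Adverse events and other unintended effects of interventions during the intervention period will be spontaneously reported". It fixes both the mode (spontaneous) and the window (the intervention period). The Discussion gives the length of that period when it explains the choice of endpoint: "we choose the short-term (1-month) outcome as the primary outcome based the intervention period (four weeks". The Abstract and the description of the quitline arm also give four weeks.

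The gum is described under Other interventions: "All participants will receive a 4-week supply of NRT gum by mail (300 pieces". The dosing instruction is: "Participants will be directed to use the gum as needed when they encounter situations or cues that tempt them to smoke". The text gives no daily dose, no stop date, and nothing about returning or discarding leftover pieces.

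Under Participants and recruitment, two entry criteria bear on how fast and how soon the gum is used: "currently smoke at least 5 cigarettes per day" and "willing to make a quit attempt within 1 month". Follow-up contacts are planned at 1, 3, 6 and 12 months. After week 4 both arms keep reactive counselling for a year.

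**The concern.** The window for recording events is tied to a calendar period, while exposure to the trial-supplied drug is tied to how fast each person works through a fixed number of pieces. The two end together only at one average rate of use. Below that rate, or with a late start, exposure continues after the rule has stopped asking for events.

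At stake is how complete the safety record is for nicotine gum supplied by the trial. The protocol treats nicotine safety as relevant: it excludes people with conditions that preclude nicotine replacement, and the Data management section gives the data monitoring committee a safety role. Informal reporting after week 4 might also differ by arm. Table 1 gives the WQ mini-program a function that asks about side effects of medication, and no matching feature is described for the quitline arm.

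**Working it through.** **Inputs from the protocol article**
- Gum supply: 300 pieces, labelled as four weeks (Other interventions).
- Reporting window: four weeks, taken as 28 days (Follow-up measures with Discussion).
- Minimum consumption at entry: 5 cigarettes a day (Participants and recruitment).
- Contacts: 1, 3, 6 and 12 months (Follow-up measures).

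**Inputs that are assumptions**
- Daily gum use, which is not stated and is shown as a range.
- A start on day 7 as an example of late delivery or late first use.
- Three months taken as about day 90.

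**Step 1. The rate implied by the plan's own label.** 300 / 28 = 10.7 pieces a day, used from day 0. At this rate supply and window end together.

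**Step 2. Late start.** If the first piece is used on day 7, finishing by day 28 needs 300 / (28 − 7) = 300 / 21 = 14.3 pieces a day.

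**Step 3. How long the supply lasts from day 0.** Duration = 300 / daily use; pieces left at day 28 = 300 − 28 × daily use.

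| Assumed pieces a day | Supply lasts (days) | Left at day 28 |
|---|---|---|
| 15 | 20 | 0 |
| 12 | 25 | 0 |
| 10.7 | 28 | 0 |
| 8 | 37.5 | 76 (25%) |
| 5 | 60 | 160 (53%) |
| 3 | 100 | 216 (72%) |

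The row for 5 a day would describe a smoker at the entry minimum who uses one piece per cigarette. The protocol contains no such rule, so the row is only an illustration.

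**Step 4. Whether a late start is plausible.** Participants need only be willing to try to quit within a month. Table 2 puts the setting of a quit day in week 2 of the WQ programme. The gum comes by mail. The mini-program's daily messages run for four weeks from the quit date, so a quit date on day 7 would carry them to day 7 + 28 = day 35. In the WQ arm, then, even the end of the intervention period depends on what it is counted from.

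**Step 5. What the existing contacts would cover.** The supply lasts to day 90 at 300 / 90 = 3.3 pieces a day. A gum-use question at 3 months therefore spans the whole supply for anyone averaging at least 3.3 a day from day 0.

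**The case against.** The strongest reply is that the intended windows agree: gum labelled as four weeks' worth, an intervention of four weeks, and events recorded during it. That is right as far as intent goes. A reader might infer that the protocol contradicts itself, and it does not. What remains is that as-needed use does not enforce the label.

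A second reply is that this is a condensed article. Table 3, which holds the full list of measurements, is not shown, and neither are the mailed instructions. Either could give later time points for adverse events or a stop date for the gum. This stands as a limit on the point. Still, the sentence under Follow-up measures states a window positively; it is not merely silent. If later capture exists, the sentence should match it.

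A third reply is that every rate other than 10.7 a day is assumed. That also stands. A reader might infer that light smokers will typically have about half their gum left at day 28. The documents do not support this, because the 53% figure needs one piece per cigarette, and the protocol ties use to temptation and cues instead.

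Finally, the gum is the same in both arms and is not the randomised comparison, and the window covers the start of use for anyone who begins within four weeks. This keeps the consequence small. Reactive counselling gives people a chance to mention a later event, but the stated rule does not require that it be recorded.

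**Conclusion.** The point holds in a limited form. As worded, adverse-event reporting ends with the four-week intervention period, while trial gum outlasts day 28 for anyone averaging under about 10.7 pieces a day from day 0, or under 14.3 a day if starting on day 7. The number of participants this describes cannot be worked out from the article.

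The conclusion rests on the published wording on gum and on adverse events, on counting the four weeks from day 0, and on neither Table 3 nor the mailed instructions already closing the gap. It would be too strong to say that safety events will be lost, or that the trial result is put in doubt. Later events may still be mentioned, and the primary outcome, sample size and power do not depend on the reporting window. This is a small, worthwhile improvement to the safety rule.

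**What to change.** Reword the sentence under Follow-up measures so that adverse events are recorded, in both arms, until the end of the intervention period or the last use of trial gum, whichever is later. Keep spontaneous reporting as the mode. At the existing 1- and 3-month contacts, ask whether trial gum is still being used and the date of the last piece. Gum-use data are needed anyway, because the subgroup analyses in the Statistical analysis plan section name use-of-intervention variables, "including compliance of using NRT gum".

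A direct adverse-event question at 3 months is optional. If it is added, put it in identical words to both arms and report solicited events separately from spontaneous ones.

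The cost is a wording amendment during recruitment, a few extra items at contacts already scheduled, some recall error in the last-use date, and slightly more event data to code. The direct question would also bring in a second mode of ascertainment. No change to the sample size or the primary analysis is needed. If Table 3 or the mailed instructions already set later time points or a stop date, it is enough to bring the sentence into line with them.
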